
### Study subjects

Patients with NAFLD attending the polyclinic of the NIOC Central Hospital in Tehran are to be invited to the study. The patients will be diagnosed by a radiologist and a hepatologist as having fatty liver, using ultrasonography. Patients should meet the eligibility criteria. After their identification, the patients will be referred to the principal investigator.

First, the goals, methods, and benefits of the intervention will explained and Informed Consent Forms signed. The general questionnaire, short-form International Physical Activity Questionnaire (IPAQ) and 24-h food recall questionnaire are to be completed by interviews. Necessary education and guidelines concerning lifestyle modification, will then be given [45], including a weight-loss diet (5% weight loss during the study [50]) and increasing physical activity (aerobic with moderate intensity, at least 3 times per week, 30–45 min [51]).

Anthropometric measurements, including weight, height and waist circumference are to be assessed by using a digital scale, stadiometer, and nonelastic tape, respectively.

A 24-h food recall questionnaire is to be completed at the beginning, after 1.5 months, and at the end. Blood pressure (systolic and diastolic) will be measured at the beginning and the end with a manometer. Ten milliliters of blood at the beginning and 10 ml at the end are taken from a peripheral vein after a 12-h overnight fast. After centrifuging for 20 min (3000 *g*), the serum samples will be frozen simultaneously and stored at −80 °C until analyzed. At the end, the evaluated outcomes are to be presented to the patients privately.

### The sample size

The sample size was calculated using the “two mean comparison formula” and was related to a previous study [52] which had assessed the effects of cardamom on lipid profiles. In this study, the errors I and II are considered to be 0.05 and 0.2, respectively. The mean difference of TG between the groups was 5 mg/dl, and the standard deviation of each group was 8 mg/dl. The sample size was determined to be 40 subjects in each group. In total, 80 patients were invited and randomly divided into two groups as follows:Forty overweight or obese patients with NAFLD will be given lifestyle change recommendations (weight-loss diet (5%) during the study and increasing physical activity) and a green cardamom supplement for 3 monthsForty overweight or obese patients with NAFLD will be given lifestyle change recommendations (weight loss diet (5%) during the study and increasing physical activity) and a placebo supplement for 3 months

## Randomization and intervention

Patients are divided into two equal groups using block randomization. Stratified randomization will be used to control age and gender distribution. In this study, the ratio of green cardamom and placebo supplementation groups is 1:1. The block randomization is performed by an assistant and the intervention allocation is blinded for both the investigator and subjects. The participants are randomly placed into two groups receiving whole green cardamom powder or toast powder supplements. Cardamom and placebo capsules are prepared by the Traditional Medicine Research Center (TMRC), Iran University of Medical Sciences. Each capsule contains 0.5 g of whole green cardamom or toast powder. Placebo and cardamom capsules are similar in shape, size, and color. At the beginning of the study, all placebo capsules are to be placed near the cardamom capsules so that the patients are able to smell them. Even though some cardamom volatile oils may be absorbed by the placebo capsules, this amount is considered negligible compared to the amounts that affect health indicators. The type of supplements is blinded as A and B packages for investigators and patients.

According to previous trials, the dose of whole green cardamom powder was determined to be 3 g per day [46, 52, 53]; two capsules were consumed with each meal.

The voucher number of green cardamom is *Elettaria cardamomum* (L.) Maton, Family: Zingiberaceae, PMP-669. An essential oil percentage and the total content of phenolic and flavonoid compounds of green cardamom will be assessed using high-performance liquid chromatography (HPLC) and gas chromatography mass spectrometry (GC-MS) in the institute of medicinal plants, Shahid Beheshti University of Medical Sciences, Tehran, Iran. Some polyphenolic compounds of green cardamom, whose effects have been mentioned in other articles (caffeic acid, gallic acid, quercetin and luteolin), will also be determined by using HPLC.

Supplements are to be distributed among patients once a month and their potential complications and consumption processes registered (number of consumed capsules and the returned packages). In addition, the consumption process is to be checked once a week, by telephone.

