Lifestyle changes—including gradual weight loss and increasing physical activity—are common ways to reduce and treat NAFLD [39–43]. Since achieving weight loss and maintaining a reduced weight for a long time is difficult [44], it seems that dietary changes may be a proposed therapeutic approach for these patients [45]. Some studies were conducted on green cardamom’s role in health as a spice. The effects of cardamom reported by those studies are blood pressure lowering, fibrinolysis enhancing, antispasmodic effects, and gastroprotective, antibacterial, antioxidant [46], anti-inflammatory, anti-food poisoning, carminative, diuretic, expectorant, heart-function improving, anticarcinogenic [47], and antiplatelet aggregation effects [48]. Cardamom volatile oil contains terpenes, esters, flavonoids and other compounds. The major constituents of the volatile oil of cardamom include about 36% 1,8-cineole, 31% alpha-terpinil acetate, 12% limonene, 3% sabinene and others. Most studies have been conducted on the 1,8-cineole compound. The reported effects are apoptotic, the inhibiting of cytokines, prostaglandins, leukotrienes, and nitric oxide (inhibition of cyclooxygenase-2 (COX-2) and inducible nitric oxide synthase (iNOS)), TNF-α and IL-1β inhibition, liver necrosis reduction, cardiovascular effects (blood vessel relaxation), as well as anticholinergic effects and the blocking of muscarinic receptors [49].

The hypothesis is that the antioxidant, anti-inflammatory, antibacterial, and hypolipidemic activities of cardamom can improve NAFLD. The effects of cardamom on Sirt1 secretion and, subsequently, PGC-1α, irisin, and insulin sensitivity are not clear. Moreover, its effects on PPAR-γ and, subsequently, serum PON1 levels need further study. With an awareness that NAFLD increases in overweight or obese populations, and the lack of human studies on the effects of green cardamom, this clinical trial study was planned to determine its impact on blood glucose indices, lipids and inflammatory profiles, liver function, and insulin resistance, especially through irisin, PON1, and Sirt1.

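### Two arm-level package codes (A and B) let one correct identification reveal the arm of every patient whose letter the observer can see

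*Protocol article*

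**What the plan says.** All the relevant text is in the protocol article, mostly under Randomization and intervention.

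- **Coding:** "The type of supplements is blinded as A and B packages for investigators and patients". No patient-specific code is described.
- **Contents:** "Each capsule contains 0.5 g of whole green cardamom or toast powder". The Background describes the aromatic fraction of the active product: "The major constituents of the volatile oil of cardamom include about 36% 1,8-cineole, 31% alpha-terpinil acetate, 12% limonene, 3% sabinene and others".
- **Matching:** "Placebo and cardamom capsules are similar in shape, size, and color". Smell is not in this list and is handled by a separate step: "At the beginning of the study, all placebo capsules are to be placed near the cardamom capsules so that the patients are able to smell". On the transfer of oil the article adds: "Even though some cardamom volatile oils may be absorbed by the placebo capsules, this amount is considered negligible". That remark compares the amount with what would affect health indicators; it does not address how well the odours match.
- **Handling:** "Supplements are to be distributed among patients once a month and their potential complications and consumption processes registered". Returned packages are counted and consumption is checked weekly by telephone.
- **Allocation:** 1:1, in blocks, with stratification for age and gender. An assistant performs it, and the investigator and subjects are blinded. Block size is not given.

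The Discussion counts the double-blind design among the trial's strengths. Trial status says recruitment was still under way.

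**The concern.** With one letter per arm, all patients in an arm share the same blind. Information from any one of them carries over to all the others with that letter. Weak clues also add up: a faint smell from one returned pack and a typical complaint from another patient both point at the same letter. With patient-specific numbers these clues would stay separate.

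The product makes clues plausible. Cardamom has a volatile oil, toast powder does not smell of cardamom by itself, and the sponsor saw enough of a problem to add an odour step. Packs are handled monthly over three months, with complications recorded alongside.

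Knowledge of arm could influence the ultrasound grade, the interviewed food recall and activity questionnaire, how complications are elicited, and how firmly lifestyle advice is delivered. It could also influence two decisions: the adherence-based exclusion (Exclusion criteria) and the replacement of uncooperative patients, which the Discussion foresees.

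**Working it through.** **1. Number of patients.** The sample size section gives a difference of 5 mg/dl, SD 8 mg/dl, errors 0.05 and 0.2, and 40 per group. Check: n = 2 × [8 × (1.960 + 0.842) / 5]² = 40.19 per group (two-sided), which agrees with 40 to within rounding. The total of 80 is used below only as a count; the blinding point does not depend on the power calculation.

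**2. Exposure from one correct identification.** Take an observer who sees every pack.
- Two codes: 80/80 = 100% of allocations revealed.
- One code per patient: 1/80 = 1.25%.

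An observer who sees only some of the letters learns the arms of those patients only.

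**3. How easily one identification could occur.** The article gives no recognition rate, so p is an assumption: the chance that a given cardamom patient's pack is correctly recognised, independently across the 40. The chance of at least one recognition is 1 − (1 − p)^40. The expected number of patients exposed by the end is 80 times that with two codes, and 40p with unique codes.

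| Assumed p | At least one recognition | Expected exposed, two codes | Expected exposed, unique codes |
|---|---|---|---|
| 1% | 33.1% | 80 × 0.331 = 26.5 | 0.4 |
| 5% | 87.1% | 80 × 0.871 = 69.7 | 2 |
| 10% | 98.5% | 80 × 0.985 = 78.8 | 4 |

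If placebo packs could be recognised too, the chance of at least one recognition among 80 is 55%, 98% and over 99.9%. The two-code column is an upper case, because it supposes one observer who sees all letters and whose identification is correct.

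**4. Later allocations.** Suppose the observer also sees all earlier letters within a stratum and knows the block size b and where blocks begin. By enumeration of permuted 1:1 blocks, the share of assignments known with certainty is 2/(b + 2).

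| Assumed b | Known with certainty | Best-guess hit rate |
|---|---|---|
| 2 | 50% | 75% |
| 4 | 33% | 71% |
| 6 | 25% | 68% |
| 8 | 20% | 67% |

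These figures are conditional. Block size is not stated, and stratification by age and gender means each stratum would have to be followed separately if blocks run within strata.

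**5. Which outcomes are open to influence.** The Objectives list serum lipids, glucose indices, inflammatory factors, PON1, Sirt1 and irisin. Measurements and assessments assigns these to analysers and ELISA kits, or to formulae from such values, so reading bias is unlikely. An indirect route remains: both arms receive weight-loss and exercise advice, and the article relies on identical prescriptions to control diet and activity. Uneven coaching could therefore reach lipids and glucose. The documents give no size for this.

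**The case against.** The strongest reply has five parts.

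- **Patients.** A patient normally sees one letter. A reader might infer that one guess by anyone unmasks the whole trial. The text does not support that: trial-wide exposure needs an observer who sees many letters, or patients who compare packs. A guess also does not confirm itself. This stands, and limits the point mainly to staff.
- **Staff.** The article does not say who dispenses, telephones or registers complications. Ultrasound belongs to one radiologist and lifestyle advice to a dietician; neither is said to handle packs. This stands: the route to those outcomes is possible, not shown.
- **Odour step.** A reader might infer that odours are matched only at the start and fade before later dispensing. The text gives a start for a step that covers all placebo capsules, and no end. Continuous co-storage is as natural a reading, and nothing documents fading. Only a request for clarity remains.
- **Prediction.** A reader might infer that upcoming assignments are predictable. That needs an unstated block size, visible earlier letters and tracking of strata, and an assistant handles the randomization. It remains a conditional risk.
- **Condensed article.** Kit numbering, storage and code custody are often left to a full protocol. That would answer a complaint about missing detail, but the A/B coding is stated outright as the blinding method.

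It can also be said that a recognisable smell would betray packs one by one even under unique numbers. That is true, but each recognition would then expose one patient, and clues would not add up across patients.

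**Conclusion.** The point holds in limited form. The article fixes a two-code blind for an aromatic product that is handled repeatedly, and this is weaker than it needs to be. One correct link between letter and arm reveals every allocation whose letter the observer can see, up to 80 of 80, instead of 1 of 80. The contrast measures how fragile the blind is; it is not an estimate of bias in any outcome, and the recognition rates behind the table in the working are assumed.

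The gain from a change lies mainly in ultrasound grading, diet and activity interviews, complication reporting, even delivery of lifestyle advice, and adherence or replacement decisions. The serum assays that make up the stated objectives are largely protected from assessor bias. Neither loss of the odour match over time nor predictability of later allocations is established by the document. No sample size figure changes.

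**What to change.** 1. Have the capsule preparer label each pack with a unique participant or kit number. The list linking number to arm should be held away from the clinic, by the preparer or by the randomising assistant.
2. Drop the A and B letters on all packs not yet dispensed, including the remaining monthly packs of patients already enrolled. Relabelling cannot undo what staff have already seen, but it stops further clues from adding up.
3. State that placebo and cardamom capsules stay co-stored until each monthly dispensing, or say so explicitly if that is already the practice.

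The cost is some extra packing and labelling work and the upkeep of a code list. Longer co-storage could let the placebo take up a little more oil, an uptake that the article already judges negligible for health indicators. Product, visits and sample size are unchanged.

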## Abstract

**Background:**

The relationship between dietary components and nonalcoholic fatty liver disease (NAFLD) needs to be further investigated. The potential health benefits of cardamom have been found in some studies. Cardamom showed beneficial effect on hepatomegaly, dyslipidemia, and fasting hyperglycemia in animals. However, some adverse effects of cardamom have been reported in animals. No previous human study had been conducted on the effects of cardamom in NAFLD. This study aims to determine the effects of green cardamom (*Elettaria cardamomum*) supplementation on blood glucose indices, lipids, inflammatory profiles, and liver function, especially by examining irisin, paraxonase-1 (PON1) and sirtuin-1 (Sirt1) in obese patients with NAFLD.

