### Objectives

× Compare the mean serum lipid (triglycerides (TG), total cholesterol (TC), low-density lipoprotein (LDL), high-density lipoprotein (HDL)) and glucose indices (fasting blood sugar (FBS), fasting blood insulin (FBI), homeostasis model assessment-insulin resistance (HOMA-IR), Quantitative Insulin Sensitivity Check Index (QUICKI)) between the two groups and within each group, before and after intervention× Compare the mean serum inflammatory factors (TNF-α, interleukin-6 (IL-6), highly sensitive C-reactive protein (hs-CRP)) between the two groups and within each group, before and after intervention× Compare the mean of serum PON1, sirt1, and irisin between the two groups and within each group, before and after intervention

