## Discussion

This trial will first assess the effects of green cardamom (*Elettaria cardamomum*) on blood glucose indices, lipids, inflammatory factors, paraxonase-1, sirtuin-1 and irisin in overweight or obese patients with nonalcoholic fatty liver disease (NAFLD). The different clinical usages and the lack of awareness concerning the advantages and disadvantages of green cardamom in patients with NAFLD makes this study very pertinent. Although there is a hypothetical reason for using green cardamom in the treatment of some disorders, its therapeutic use in humans necessitates the study of its potential in different diseases, particularly NAFLD. Attention should be paid to the increasing rates of obesity (and, consequently, NAFLD). Due to remarkable changes of some blood markers in this population, and the lack of human studies on the effects of green cardamom, this trial selected these patients as the most suitable cases for intervention.

The strengths of the study are its randomized double-blinded design, protocol publication, the measurement of dietary outcomes and physical activity status, and the recording of patient-reported probable complications.

The limitations of the study are self-reporting of diet and physical activity, slow patient recruitment because of the eligibility criteria, a single center and lack of cooperation by some patients at the end, which may lead to these patients needing to be being replaced.

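### Harms are registered at the monthly capsule distribution although every patient is phoned weekly; one open question at those calls would shorten recall and firm up the by-arm description of harms

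*Protocol article*

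**What the plan says.** Under Randomization and intervention, the protocol article sets out when harms are noted: "Supplements are to be distributed among patients once a month and their potential complications and consumption processes registered". The parenthesis that follows concerns counts of capsules taken and packages returned. The next sentence describes the weekly contact: "In addition, the consumption process is to be checked once a week, by telephone". No other content is given for that call.

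The Discussion lists among the trial's strengths "the recording of patient-reported probable complications", and argues that "the lack of awareness concerning the advantages and disadvantages of green cardamom in patients with NAFLD makes this study very pertinent". The Background paragraph of the abstract says that "some adverse effects of cardamom have been reported in animals".

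The Objectives section has three items: lipids and glucose indices, inflammatory factors, and the three mechanistic markers ("Compare the mean of serum PON1, sirt1, and irisin between the two groups and within each group, before and after intervention"). None mentions complications. Data analysis names a chi-square test for baseline characteristics and a repeated measures analysis of variance for the dependent variables. It does not say how registered complications are summarised.

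**The concern.** The article fixes both the occasion for registering harms and the purpose of the weekly call, so this is more than silence on a detail. The more frequent contact is given a compliance task and the less frequent one carries the harms. A mild symptom that comes and goes between two distributions has to be remembered for up to a month. Staff will meanwhile have spoken to the patient several times with no stated duty to ask about it.

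The wording also leaves open what counts as an entry. The methods speak of *potential* complications and the Discussion of *probable* ones. Either word could be read as any complication that may occur, or as one that someone already suspects the capsule of causing. Staff who read it differently would record different things. If the second reading were applied, a patient's guess about an aromatic product could influence what is reported.

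At stake is the quality of the harms information from what the article presents as the first trial of cardamom in this patient group.

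**Working it through.** **Contacts and recall.** Inputs: 3 months of treatment, monthly distribution and a weekly call (Randomization and intervention).

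- Three months is about 13 weeks, so weekly contact gives about 12 to 13 contacts, depending on whether the final week is a call or the end visit.
- Monthly registration gives about 3 points (months 1, 2 and 3). This assumes that complications are also registered when the last packages come back; if they are not, it is 2.
- The longest recall is about 30 days at monthly registration and 7 days at weekly contact, a ratio of 30/7 = 4.3. If events fall evenly over the interval, mean recall is 30/2 = 15 days against 7/2 = 3.5 days.

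These figures describe opportunity to ask. They do not estimate how many events are missed, and the article gives nothing from which to estimate that.

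**What 40 per arm can support.** The planned size is for triglycerides (The sample size): difference 5 mg/dl, SD 8 mg/dl, errors 0.05 and 0.2. Two-sided, n = 2 × [8 × (1.960 + 0.842)/5]² = 40.19 per group. That agrees with the stated 40 to within rounding (41 if rounded up). The size was not chosen for harms.

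The article gives no complication rates, so the following rates are assumptions. The chance of seeing at least one event among 40 patients is 1 − (1 − p)^40:

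| True rate p | Chance of at least one event |
|---|---|
| 1% | 33% |
| 2% | 55% |
| 5% | 87% |
| 10% | 99% |

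Power for a two-sided 0.05 comparison of proportions is Φ[(d − 1.96 × SE₀)/SE₁], where d is the difference, SE₀ uses the pooled rate and SE₁ the separate rates:

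| Placebo vs cardamom | Power at 40 per arm |
|---|---|
| 5% vs 10% | 13% |
| 5% vs 15% | 32% |
| 5% vs 20% | 53% |
| 5% vs 30% | 85% |

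For 5% vs 15%: d = 0.10, SE₀ = √(2 × 0.10 × 0.90/40) = 0.0671 and SE₁ = √[(0.05 × 0.95 + 0.15 × 0.85)/40] = 0.0661. Then (0.10 − 0.1315)/0.0661 = −0.48 and Φ = 0.32. The 95% CI for that risk difference would be about ±1.96 × 0.0661 = ±13 percentage points.

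Common complications would therefore be seen and could be tabulated by arm, but a test would show only a large excess. Any comparison of harms is descriptive, however the events are collected.

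**The case against.** There is a good case for the article as it stands.

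- **It is a condensed account.** The wording of the harms question, event definitions, relatedness rules and harms tables commonly sit in a full protocol, manual or analysis plan. Their absence here is not a fault. This stands, so the point is confined to the schedule the article does fix.
- **The call may do more than the sentence says.** Nothing states that a complaint raised on the phone goes unrecorded, or that patients cannot report between visits. This also stands. What remains is that asking is not described as part of the call, so capture there would depend on patient or caller.
- **Harms can still be compared.** Allocation is 1:1 and blinded against placebo, and the placebo capsules are kept near the cardamom to share its smell. ALT, AST and blood pressure are measured at the beginning and the end in both groups, and the time × treatment analysis covers all dependent variables. This stands. These measures do not depend on recall, but they cannot show a symptom that has resolved before the end visit.
- **Monthly collection over 3 months is defensible.** It is. The argument for change is that the better schedule is nearly free.

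Three stronger readings are tempting and not supported. A reader might infer that the trial cannot answer its own question about disadvantages; but disadvantages appear as rationale in the Discussion and not among the objectives, and a by-arm table needs no listed objective. A reader might infer that only events attributed to the capsule are recorded; but that rests on the loose words *potential* and *probable*, and no causality rule is stated. A reader might take the limits after zero events in 40 patients, 1 − 0.05^(1/40) = 7.2% one-sided or 1 − 0.025^(1/40) = 8.8% two-sided, as the size of the defect; but they follow from n = 40 and would be the same after the change.

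**Conclusion.** The point holds as a worthwhile, low-cost improvement and not as an error that invalidates anything. As described, harms are sought at about 3 points with up to about 30 days' recall, when 12 to 13 contacts at 7-day intervals are already planned. This sits poorly with an article that cites unknown disadvantages and animal adverse effects as motivation and claims complication recording as a strength. The effect is a weaker by-arm description of harms, not the loss of one.

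The conclusion assumes that the weekly call is run as the sentence describes it and that no fuller document already adds a symptom question. If one does, only the article's wording needs to be aligned. Neither the size nor the direction of any under-count can be derived from the article.

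**What to change.** In Randomization and intervention, state that the weekly call and the monthly visit each ask one identical open question in both arms: whether the patient has had any new symptom or illness since the last contact. State that every event is recorded with its date, whether or not it is thought related to the capsule. That also settles the ambiguity between *potential* and *probable*; the Discussion wording should be changed to match.

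Report the number of patients with at least one event by randomised arm, with a risk difference and 95% CI, labelled as descriptive given 40 per arm.

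The cost is one extra question in contacts already scheduled, one form and one table. The downside is that more trivial events will be recorded. Trial status says recruitment was ongoing at submission, so if the change comes mid-trial it should start on the same date in both arms and that date should be recorded.
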